### 2.6. Evaluation of System Performance

To assess the reproducibility of TDS, tongue images will be taken twice with a 30 min interval. Considering inevitable variations in length, angle, and shape of the protruding tongue in taking images, it will be necessary to have an appropriate interval between the two examinations to more accurately investigate the reproducibility of TDS. A 30 min interval will be able to prevent patients from intentionally protruding their tongues as they had done in the first examination. Then, we will compare TCT as shown on two different images for each patient.

After two examinations of TDS, we will measure the weight of the tongue coating with a method described by Yaegaki and Sanada [13] to analyze the correlation between the real quantity of tongue coating and the percentage of coating measured with TDS. The coating will be collected from each patient by the following procedure: first, cotton rolls will be put around the tongue to remove moisture; then, saliva on the dorsal surface of the tongue will be removed with a stream of air and pure pulp tissue paper; finally, the coating will be carefully collected with a tongue scraper from the terminal sulcus to the apex of the tongue; and the tongue dorsal surface will be cleaned with cotton pellets immersed in physiological saline. The weight of the coating will be then measured with a microbalance.

### 2.7. Conventional Method for Evaluating Tongue Coating Thickness

In the conventional method of tongue diagnosis, including the evaluation of tongue coating, a practitioner directly examines the tongue from the tip to the root. TCT is described as either no, thin, or thick coating. No coating literally means the absence of tongue coating; thin coating is diagnosed when the body of the tongue is barely visible; and thick coating when the body of the tongue cannot be seen at all [3].

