## Abstract

Tongue diagnosis is an important procedure in traditional Korean medicine (TKM). In particular, tongue coating thickness (TCT) is deemed to show the progression of the disease. However, conventional tongue diagnosis has limitations because of various external factors. Therefore, it is necessary to investigate the availability of tongue diagnosis system (TDS) in the assessment of TCT. This study has been designed as a prospective clinical trial involving 60 patients with functional dyspepsia. Tongue images will be obtained by TDS twice with a 30 min interval. The system will measure the percentage of TCT and classify it as either no coating, thin coating, or thick coating according to the existing diagnostic criteria. After finishing the collection of 60 patients' tongue images, TCT on the images will be simultaneously evaluated by the conventional method to establish the gold standard for assessing TCT by 5 well-trained clinicians. The evaluation will be repeated by the same clinicians after 2 weeks, but the order of the images will be changed. This trial is expected to provide clinical evidence for the availability of TDS as a diagnostic tool and to contribute to the standardization of the diagnosis system used in TKM. This trial is registered with ClinicalTrials.gov NCT01864837.

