## 1. Introduction

Tongue diagnosis is an important diagnostic procedure that is used in traditional Korean medicine (TKM) to examine the physiological function and pathological changes of the internal organs. It involves the examination of the body of the tongue (its color, shape, moisture, and movement) and the coating on the tongue (its color, thickness, distribution, and characteristics at the root) [1, 2]. The coating is believed to reflect the condition of the stomach as well as the nature and the site of the pathogenic factors. In particular, tongue-coating thickness (TCT) is considered to reflect the progression of a pathological condition [3]. A conventional method used in tongue diagnosis involves direct examination of a protruded tongue by a practitioner, so the result is not only affected by his or her subjectivity but also by environmental factors such as light [4]. Moreover, the available diagnostic criteria are insufficient and vague. 

To overcome the above limitations, a number of tongue diagnosis systems (TDSs) have been developed in recent years [5]. In general, TDS has a number of components including image capturing and storage, color correction, tongue segmentation, and image analysis. The processes of image capturing and storage are hardware resources, while those of color correction and tongue segmentation are image-preprocessing steps in tongue diagnosis. In the process of image analysis, the tongue is classified according to selected diagnostic parameters [5, 6]. In this study, tongues will be classified based on the measurement of TCT into those with no coating, thin coating, or thick coating according to the criteria developed by Kim et al. [7].

Functional dyspepsia (FD) is chronic or recurrent dyspepsia without evidence of organic disease [8]. The prevalence of FD is from 11.5% to 14.7% in the general population in Western countries [9], while in Republic of Korea, 25% of the population is affected as shown by a recent epidemiological survey [10]. We decided to include patients with FD in our study, because according to TKM, FD is one of the common stomach diseases that are well reflected by various features of tongue coating [11, 12]. 

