For the objective and standardized tongue diagnosis system in TKM, it is necessary not only to develop an objective diagnostic tool but also to propose a new study protocol for clinical trial. We aimed to investigate the agreement between the results provided by TDS and those obtained by the conventional method in the assessment of TCT, which constitutes a part of tongue diagnosis in TKM, for evaluating on the availability of TDS in practice.

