### 2.8. Establishment of Gold Standard

To establish the gold standard for the assessment of TCT, 5 clinicians with 5 or more years of clinical experience and working at the Korean Medicine Hospital of the Kyung Hee University will be included in the trial to assess the images obtained by TDS. Before participation in the study, they will augment their knowledge about conventional methods of TCT assessment and be well trained in TCT differential criteria to obtain a reliable gold standard. The images will be sequentially presented to the clinicians using a picture-viewer software and an LCD monitor (DN-50PZ66, 50′′ HD, 1366 × 768 resolution, LG, Korea). Each image will be displayed for 10 seconds (10 minutes in total). Clinicians will be expected to label each image as either “no coating,” “thin coating,” or “thick coating.” Their assessment will be considered as a gold standard, and if there is a disagreement, we will choose the majority as the final diagnosis. All assessments will be performed individually in the same room and under the same conditions (in terms of brightness and distance between the clinician and the monitor). Clinicians will be blinded to the assessment of other clinicians and clinical data of the patients. The assessment will be repeated after 2 weeks and will involve the same clinicians, but the images will be presented in a changed order. The comparison of the 2 assessments will allow us to analyze the intra- and interrater reliability of the clinicians.

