## 3. Discussion

Tongue diagnosis is an important procedure in TKM, but conventional methods are limited by various external factors [4]. In an attempt to overcome these limitations, different types of TDSs have been recently developed [5]. The current study has been designed to investigate the availability of a newly developed TDS in the measurement of TCT by assessing the agreement between the results obtained by TDS and those obtained by well-trained clinicians as a gold standard. There have been several studies investigating diagnostic agreement and then emphasizing the importance of a training process based on the diagnostic criteria. Zhang et al. [15] showed in their clinical research that the training focused on a consensus of the traditional Chinese medicine (TCM) diagnostic criteria improved the agreement of TCM diagnosis in patients with rheumatoid arthritis. Son et al. [16] also investigated the importance of training in TCT assessment for the standardization of TKM tongue diagnosis. In their study, the agreement of TCT assessment among 15 clinicians after training was higher than that before training, and the agreement between TCT assessment and the value of TDS after training was also higher than that before training. Furthermore, the difference in agreement before and after training was significant (*P* < 0.05). Therefore, in the present study, to establish a reliable gold standard for TCT assessment and to improve diagnostic agreement, 5 clinicians will be sufficiently trained on the basis of TCT differential criteria by Kim et al. [7]. To our knowledge, this has been the first trial to compare TDS with a conventional method in the assessment of TCT for patients with FD. In addition, our study has been designed to investigate the reproducibility of TDS to provide a rationale for its wider use in clinical practice. Finally, the trial is expected to confirm the availability of TDS as an objective diagnostic tool. We believe that our results will contribute to the standardization of the diagnosis system used in TKM.

The study was designed in 2013. The first participant was enrolled in February, 2013. The recruitment of participants is ongoing. In addition, we have already finished the clinical trial registration (ClinicalTrials.gov NCT01864837).

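### The primary kappa compares TDS software with clinicians' reading of TDS images, not with the conventional method as the article defines it

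*Protocol article*

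**What the plan says.** The article describes the conventional method twice in the same sense. The Introduction says "A conventional method used in tongue diagnosis involves direct examination of a protruded tongue by a practitioner". Section 2.7 says "a practitioner directly examines the tongue from the tip to the root".

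The reference standard is different. In section 2.8 five clinicians "will be included in the trial to assess the images obtained by TDS". They work from an LCD monitor: "Each image will be displayed for 10 seconds (10 minutes in total". Sections 2.1 and 2.2.1 likewise have clinicians grade images.

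The name of the conventional method is nevertheless attached to this reading and to the conclusions:

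- Abstract: "TCT on the images will be simultaneously evaluated by the conventional method to establish the gold standard".
- Aim, at the end of the Introduction: "the agreement between the results provided by TDS and those obtained by the conventional method", in order to judge the TDS for use in practice.
- Discussion: "this has been the first trial to compare TDS with a conventional method in the assessment of TCT", in functional dyspepsia.

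Section 2.9 analyses the primary outcome with Cohen's kappa between the TDS class and the clinicians' final diagnosis.

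**The concern.** One term covers two procedures, and the conclusion is drawn for the one that is not carried out. The Introduction motivates the TDS by the dependence of direct examination on the practitioner and on light. Section 2.3 describes a device that shuts out external light and illuminates the tongue evenly. Clinicians who read its photographs therefore work under the device's own correction of that weakness.

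At stake is what the primary kappa can be quoted for. Section 2.6 accepts that length, angle and shape of the protruded tongue vary between images. If software and readers grade the same photograph, a capture that makes the tongue look more coated to both moves both gradings together and leaves kappa unharmed. A reader who takes the aim at its word would then credit the TDS with agreement with bedside examination that was never tested.

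**Working it through.** **1. The texts side by side.** Definition (Introduction, section 2.7): direct examination of the tongue. Procedure (Abstract, sections 2.1, 2.2.1, 2.8): reading of TDS images. Aim and Discussion: comparison with the conventional method. No section has a clinician grade coating thickness on the patient. The article states both the definition and the procedure, so condensation for a journal does not explain the difference.

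**2. How many images are read.** 10 min × 60 s ÷ 10 s per image = 60 images, for 60 patients. This reproduces the stated 10 minutes and implies one image per patient, although two are taken. That the image read is the one the TDS scored is the natural reading of section 2.2.1, but it is not stated outright.

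**3. Illustrative size.** From the article: cutoffs 29.06% and 63.51% (section 2.5) and five readers (section 2.8). All else is assumed:

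- true coverage T ~ N(46, 20²), clipped to 0–100;
- capture error c ~ N(b, s²), with s = 3, 5 or 8 points;
- TDS class: T + c, cut at the two cutoffs;
- reader of the image: T + c + e; direct examiner: T + e; e ~ N(0, 10²), same cutoffs;
- median of five readers, standing in for the majority;
- kappa = (p_o − p_e)/(1 − p_e), with p_o the observed and p_e the chance agreement.

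Results without bias (b = 0), one million simulated patients per row:

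| Capture SD | Same image (planned) | Direct examination | Difference |
|---|---|---|---|
| 3 | 0.792 | 0.761 | 0.031 |
| 5 | 0.796 | 0.716 | 0.080 |
| 8 | 0.805 | 0.635 | 0.170 |

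The planned kappa hardly moves as capture error grows, whereas kappa against direct examination falls.

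With a systematic device bias, at capture SD 5:

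| Bias (points) | Same image | Direct examination | Difference |
|---|---|---|---|
| 0 | 0.80 | 0.72 | 0.08 |
| +5 | 0.80 | 0.66 | 0.14 |
| +10 | 0.80 | 0.51 | 0.29 |

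**4. Other assumptions, same direction.** With coverage SD 22 and an added TDS-only error of SD 5, same-image kappa is 0.74, 0.76 and 0.80 at capture SD 5, 10 and 20. Kappa against direct examination is 0.69, 0.58 and 0.37.

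**5. What the planned kappa does detect.** A 10-point shift in the TDS alone (capture SD 5, model of step 3) lowers same-image kappa from 0.80 to about 0.54.

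**6. What the second capture adds.** Pairing the readers' diagnosis of one capture with the TDS class of the other gives kappa 0.74/0.66/0.54 at capture SD 3/5/8. With a shared bias of 0/+5/+10 points (capture SD 5) it stays at 0.66/0.67/0.67, while kappa against direct examination falls 0.72/0.66/0.51. It responds to random capture error but not to a constant device error.

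**The case against.** The best defence is that image reading is disclosed and has reasons. The article says openly that images are graded, and the primary outcome and its analysis name the clinicians' final diagnosis, not direct examination. Photographs let five clinicians grade one stimulus under fixed conditions and grade it again after two weeks. Since direct examination is itself affected by light, a lower kappa against it would not by itself show a worse TDS. All of this stands: image reading is a legitimate reference. The fault lies in the label and the inference.

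The secondary outcomes help in part. The 30-minute repeat shows random capture variation but not a constant bias. The weight of scraped coating is independent of the image, but it is neither the conventional method nor a three-category grading.

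Three stronger readings are tempting, and the article does not support them:

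- *A reader might infer that capture error cancels out altogether.* Only errors that shift both readings alike are hidden. The a* threshold was set on images from a previous study, and an operator places the 17 nodes that outline the tongue (section 2.4). Errors in these steps act on the TDS alone and show as disagreement, as step 5 illustrates. A colour shift can also move pixels across the threshold without changing what a reader sees.
- *A reader might take the gap between same-image and cross-capture kappa, about 0.06 to 0.26 in step 6, as the overstatement.* That comparison puts independent capture error on both sides. It would apply only if direct examination carried equal, independent variation, for which the article gives no figure.
- *A reader might infer that pairing the two captures cures the fault.* Both captures come from one device, so a constant device error stays shared.

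**Conclusion.** The point holds for the label and the inference. As designed, the primary kappa supports a statement about agreement between TDS classification and clinicians' reading of TDS images. It does not support a statement about direct examination, and it is blind to capture errors that act alike on both readings. That part rests on the text alone and is firm.

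The size is illustrative. Against direct examination without bias, the planned kappa is higher by about 0.03/0.08/0.17 at capture SD 3/5/8, and by about 0.29 with a +10-point bias at capture SD 5. The coverage mean, all the SDs and the bias are assumptions. The figures also assume that software and readers see the same image and that a direct examiner uses the same cutoffs with the same reader error. The direction is the same under both sets of assumptions tried; the figures do not predict this trial's result.

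**What to change.** 1. Restate the aim (Introduction), the Abstract and the Discussion as agreement between TDS classification and clinicians' reading of TDS images, and drop the claim to compare the TDS with a conventional method. Keep section 2.7 as a description of practice, and say in section 2.8 that the reference is image reading.
2. State as a limitation that the primary kappa covers neither image-capture error common to both readings nor direct examination.
3. Optionally, say which capture is read, and pre-state a kappa that pairs the readers' diagnosis of that capture with the TDS class from the other. Label it a sensitivity check on random capture error only, not a substitute for direct examination.

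Items 1 and 2 are wording and leave the primary outcome and its analysis unchanged. Item 3 is one further 3 × 3 table from data already being collected. The article reports recruitment as ongoing, with images read only after all 60 patients are in, so it could still be fixed in advance. The price is a narrower claim and, if random capture error is present, probably a lower second kappa beside the first.

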### 2.8. Establishment of Gold Standard

To establish the gold standard for the assessment of TCT, 5 clinicians with 5 or more years of clinical experience and working at the Korean Medicine Hospital of the Kyung Hee University will be included in the trial to assess the images obtained by TDS. Before participation in the study, they will augment their knowledge about conventional methods of TCT assessment and be well trained in TCT differential criteria to obtain a reliable gold standard. The images will be sequentially presented to the clinicians using a picture-viewer software and an LCD monitor (DN-50PZ66, 50′′ HD, 1366 × 768 resolution, LG, Korea). Each image will be displayed for 10 seconds (10 minutes in total). Clinicians will be expected to label each image as either “no coating,” “thin coating,” or “thick coating.” Their assessment will be considered as a gold standard, and if there is a disagreement, we will choose the majority as the final diagnosis. All assessments will be performed individually in the same room and under the same conditions (in terms of brightness and distance between the clinician and the monitor). Clinicians will be blinded to the assessment of other clinicians and clinical data of the patients. The assessment will be repeated after 2 weeks and will involve the same clinicians, but the images will be presented in a changed order. The comparison of the 2 assessments will allow us to analyze the intra- and interrater reliability of the clinicians.

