Tongue images will be obtained with the TDS under constant conditions at the second visit. Then, the percentage of tongue coating will be measured using a TDS analysis software, and TCT will be classified with the existing diagnostic criteria [7]. To assess the reproducibility of the TDS, the images will be taken again by the same method after 30 min. After two examinations of TDS, the weight of the tongue coating (mg) will be measured quantitatively to determine the correlation with the percentage of tongue coating. 

After we complete the collection of 60 patients' tongue images, the images will be simultaneously evaluated by 5 clinicians with 5 years or more of clinical experience to establish the gold standard for the assessment of TCT. The evaluation will be repeated after 2 weeks to analyze intra- and interrater reliability of the clinicians. Finally, we will evaluate the agreement between the results provided by TDS and those obtained by clinicians. The flow of the trial is shown in Figure 1.

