### 2.2. Outcomes

#### 2.2.1. Primary Outcome

TDS will measure the percentage of tongue coating and classify TCT as either no coating, thin coating, or thick coating according to the existing diagnostic criteria [7]. At the same time, TCT shown on the images will be assessed by clinicians. We will then evaluate the agreement between the results of the TDS and the final diagnosis established by the clinicians.

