### 2.4. Image Analysis of TDS

An analysis software program of TDS was developed to analyze the percentage of tongue coating from the captured tongue images. To calculate the percentage of tongue coating, we first extract the tongue area from the captured tongue image. TDS generates 17 nodes on the tongue image on the monitor, and the operator moves the nodes on the boundary line of the tongue with a mouse. Then, the remaining area excluding the selected tongue area is removed. TDS converts the chromaticity coordinates of the extracted tongue image in the RGB color space to those in the CIE-Lab color space. The area of the tongue body is clearly more reddish than that of the coating. The positive a* value in the CIE-Lab color space is indicated by red/magenta, while the negative value by green. Therefore, tongue coating area is extracted from the entire tongue based on the difference in the a* value. The binarization threshold point of the a* value for the extraction was set through the tongue images acquired from the previous study [7] (Figure 3).

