### 2.5. Measurement of TDS

Patients press their face against the interface of the TDS, open their mouth wide, and protrude their tongue for a second. An operator who is well trained in the use of TDS makes sure that the patient's tongue does not bend or lean to one side by watching the tongue image on the monitor and takes a picture of the tongue when ready. TDS allows to measure tongue coating percentage and classify TCT into 1 of 3 categories—no coating, thin coating, or thick coating—according to the diagnostic criteria developed by Kim et al. [7]. They developed differential criteria for TCT and specifically proposed a standard for the assessment of thin and thick coatings in tongue diagnosis. In their study, 24 clinicians who were well trained and highly reliable participated in the assessment of TCT from 50 tongue images obtained by TDS, which measured the percentages of tongue coating. From an analysis of a proportional odds model, they suggested a cutoff point of 29.06% to differentiate between no coating and thin coating and a cutoff of 63.51% to differentiate between thin coating and thick coating. It takes about 5 minutes from positioning his or her tongue to obtaining the diagnosis result by TDS for each patient.

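### The readers' blinding list omits the TDS result, and nothing masks the operator to the first result when the second image is outlined by hand, so the reproducibility kappa can be inflated

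*Protocol article*

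**What the plan says.** **Readers.** Section 2.8 gives an explicit list: "Clinicians will be blinded to the assessment of other clinicians and clinical data of the patients". The TDS percentage and class are not on it, and no other section masks them. On what readers see, the same section says: "The images will be sequentially presented to the clinicians using a picture-viewer software and an LCD monitor". It does not say whether TDS output is shown or withheld. Section 2.1 has the percentage measured and the class assigned at the second visit, and the readings come later: "After we complete the collection of 60 patients' tongue images, the images will be simultaneously evaluated by 5 clinicians".

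**Operator.** Section 2.4 makes a manual step part of every TDS result: 17 nodes appear on the image and "the operator moves the nodes on the boundary line of the tongue with a mouse". The coating is then separated by a fixed rule: "The binarization threshold point of the a* value for the extraction was set through the tongue images acquired from the previous study". Section 2.5 has the operator watch the live image and choose the moment of capture, and gives the time needed: "It takes about 5 minutes from positioning his or her tongue to obtaining the diagnosis result by TDS for each patient". Section 2.1 adds the repeat: "To assess the reproducibility of the TDS, the images will be taken again by the same method after 30 min". No section says who handles the second examination, or whether that person is masked to the first.

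**Analysis.** Section 2.9 uses Cohen's kappa both for TDS against the clinicians' final diagnosis and for TDS reproducibility.

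**The concern.** The primary outcome compares two classifications of the same tongue. For the kappa to measure agreement, the clinicians' label must be formed without knowledge of the TDS label. The blinding list covers two other sources of influence and leaves out this one.

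Reproducibility has a similar gap on the machine side. Where the operator places the boundary decides which area counts as tongue, and so affects the percentage. An operator who knows the first outline and class may, without intending it, place the second boundary or time the second picture so that the results match. Section 2.6 recognises carry-over of this kind in patients: the 30-minute interval is there so that they do not deliberately repeat their first protrusion. There is no matching safeguard for the operator.

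Any such influence would favour the TDS, in a trial whose Discussion expects to confirm it as an objective tool.

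**Working it through.** **1. The plan's own figure.** Section 2.8 gives 10 seconds per image and 10 minutes in total. 60 × 10 s = 600 s = 10 min, so it reproduces. It implies one image per patient, since 120 images would take 20 min.

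**2. Order of events for the readers.** The TDS class is produced at the second visit and the readings start after all 60 patients are imaged (Section 2.1). The TDS result therefore exists before every reading.

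**3. Order of events for the operator.** The outline is a prerequisite of the result (Section 2.4), and the result comes about 5 minutes after positioning (Section 2.5). Outlining therefore falls within those minutes. The second image follows at 30 minutes: 30 − 5 = about 25 minutes during which the first result is available.

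**4. Direction and possible scale.** The documents give no error variances, so the following is an illustration only. From the documents: cutoffs 29.06% and 63.51%, five readers with a majority vote, n = 60. Assumed: true coating percentage t ~ N(46, 20), clipped to 0–100, and the errors below. Kappa = (po − pe)/(1 − pe), from 400,000 simulated patients.

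*Operator.* Observed percentage = t/(1 + e) + q, with outlining error e ~ N(0, s) and protrusion noise q ~ N(0, p).

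| s | p (points) | Independent outlines | First outline repeated exactly | Boundary moved by s if that keeps the first class |
|---|---|---|---|---|
| 3% | 3 | 0.814 | 0.832 | 0.873 |
| 3% | 6 | 0.664 | 0.674 | 0.725 |
| 6% | 3 | 0.771 | 0.834 | 0.881 |
| 6% | 6 | 0.642 | 0.678 | 0.754 |
| 10% | 3 | 0.695 | 0.836 | 0.865 |
| 10% | 6 | 0.594 | 0.683 | 0.768 |

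Exact repetition adds 0.010 (0.674 − 0.664) to 0.141 (0.836 − 0.695). Steering adds 0.059 (0.873 − 0.814) to 0.174 (0.768 − 0.594). Against the Section 2.9 bands, exact repetition crosses the 0.6 or 0.8 boundary in three of the six settings.

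*Readers.* Label error is shared at image level (SD 15 or 25) plus individual (SD 10). A share of readings follows the TDS label.

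| Image-level SD | 0% | 10% | 20% | 30% |
|---|---|---|---|---|
| 15 | 0.452 | 0.508 | 0.575 | 0.653 |
| 25 | 0.282 | 0.330 | 0.398 | 0.489 |

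The rise is 0.048 (0.330 − 0.282) to 0.207 (0.489 − 0.282). It applies only if readers know the TDS label, which the documents do not show.

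**5. Yardstick.** SE(kappa) ≈ √[po(1 − po) / (n(1 − pe)²)], with n = 60 and pe = 0.36 assumed. For kappa 0.6, po = 0.6 × 0.64 + 0.36 = 0.744, so SE = √[0.744 × 0.256 / (60 × 0.4096)] = 0.088. For kappa 0.5 and 0.7 it is 0.094 and 0.079.

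**The case against.** **Readers.** They are described as seeing images in a picture viewer, 10 seconds each, after collection ends. Clinical data might be meant to include a TDS value measured at the visit, and a condensed article may leave such detail to the full protocol. A reader might infer that the clinicians will see the TDS result because they work at the same hospital. The documents do not support that: no section shows TDS output to them or has them operate the device. Nor does the remark in Section 2.2.1, "At the same time, TCT shown on the images will be assessed by clinicians", establish it, since Section 2.1 sets out the sequence in more detail. What stands is narrower. The article chose to list the blinded items, and the list lacks the one that matters most for the primary kappa.

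**Operator.** A reader might infer that one operator does both examinations having seen the first result, so that the two measurements are dependent. The documents do not say so. Section 2.5 refers only to an operator, and using the same method does not mean using the same person. The room for influence is also limited. The a* threshold is preset, so the operator does not choose what counts as coating. The second image is a new photograph, and Section 2.6 expects length, angle and shape to vary, so a remembered outline cannot simply be copied. The larger simulated effects need active steering, which nothing in the documents suggests. All this bounds the effect, but the plan's timings still leave the first result available and no masking is stated.

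**Conclusion.** The point holds as a gap in safeguards that is cheap to close, not as demonstrated bias.

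- **Primary agreement:** the stated blinding is incomplete. Unblinding of readers is not shown.
- **Reproducibility:** the operator can know the first outline, percentage and class when capturing and outlining the second image, so the kappa can be inflated. That this happens rests on the inference that the same person, or someone who has seen the first output, handles the repeat.
- **Size:** not derivable from the documents. Under the stated assumptions, simple carry-over of the outline adds about 0.01 to 0.14 to kappa. The upper end exceeds one standard error at n = 60 and could change the interpretation band, while the lower end would be immaterial. Exact repetition is an upper case for simple carry-over, because the second tongue image differs from the first.

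**What to change.** 1. **Section 2.8:** add the TDS percentage and class to the items to which clinicians are blinded, and state that images are shown without TDS output. This costs one sentence. If the full protocol already says so, the article's list needs only that phrase.
2. **Section 2.6:** after collection is complete, outline both stored images of each patient in random order, with patient and examination number masked. Compute the reproducibility kappa from these outlines.
3. **Which outline feeds which analysis:** keep the on-the-spot class from the first examination for the primary agreement analysis. Report the on-the-spot reproducibility kappa alongside the masked one, because on-the-spot outlining is the procedure that Section 2.5 describes.

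Cost: up to 60 × 2 = 120 images, some hours of the existing operator's time. According to the Discussion recruitment is ongoing, and images already taken can be outlined again provided both have been kept, so no patient data are lost.

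Downsides: each image will carry two TDS percentages, which is why item 3 must be fixed in advance. Masked outlining also does not remove any bias in when the second picture is taken.
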